## 5. Conclusions

In conclusion, the IHD-EPITRAN study with its IHD vs. non-IHD cohort design evaluates transcriptome-wide alterations in patients’ blood RNA m^6^A and A-to-I profiles for discovery of IHD biomarkers and druggable targets. Consequently, this main goal of the IHD-EPITRAN study will be achieved via recruitment of patients from four distinct clinical cohorts, two with IHD and two without IHD, all with carefully assessed coronary status. The collected sample RNAs will be analyzed with the state-of-the-art contemporary, both quantitative and qualitative methods, for epitranscriptomic modifications in a seamless collaborative manner with experts from many disciplines, from specialist physicians to methodological experts.

## Figures and Tables

**Figure 1 ijms-22-06630-f001:**
[figure not shown]
Overview of the RNA m^6^A modification and A-to-I RNA editing and their known writers, readers, and erasers. m^6^A modification and A-to-I editing occur in most RNA species. *ADAD1-2*, adenosine deaminase domain-containing protein 1-2; *ADAR1-3*, double-stranded RNA-specific adenosine deaminase 1-3; *ADAT1-3*, adenosine deaminases acting on tRNAs; *ALKBH5*, alkB homolog 5 RNA demethylase; *A-to-I,* adenosine-to-inosine RNA editing; *circRNA*, circular RNA; *ENDOV*, human endonuclease V; *eIF3*, eukaryotic initiation factor 3; *EWSR1*, Ewing sarcoma breakpoint region 1 protein; *FMRP*, fragile X retardation protein; *FTO*, fat mass and obesity associated protein; *G3BP1*, Ras GTPase-activating protein-binding protein 1; *HAKAI*, E3 ubiquitin-protein ligase Hakai; *HNRNP-A2B1,-C,-G*, heterogeneous nuclear ribonucleoprotein A2/B1 and C1/C2 and G; *HuR*, human antigen R; *IGF2BP1-3*; The insulin-like growth factor-2 mRNA-binding proteins 1, 2, and 3; *LIN28A*, Lin-28 homolog A; *lncRNA*, long non-coding RNA; *METTL3,-14,-16*, N6- adenosine-methyltransferase catalytic subunit/non-catalytic subunit/METTL16; *METTL5*, methyltransferase Like 5; *mRNA*, messenger RNA; *miRNA*, microRNA; *Prcc2a*, proline rich coiled-coil 2 A; *RBM15*, RNA binding motif protein 15; *rRNA*, ribosomal RNA; *snoRNA*, small nucleolar RNA; *TRMT112*, TRNA methyltransferase subunit 11-2; *tRNA*, transfer RNA; *VIRMA*, vir like m^6^A methyltransferase associated; *WTAP*, Wilm’s tumor associated protein; *(YTH)DC1-2,* YTH domain-containing protein 1 ja 2; *(YTH)DF1-3*, YTH N6-methyladenosine RNA binding protein 1-3; *ZCCHC4*, zinc finger CCHC-type containing 4; *ZC3H13*, zinc finger CCCH domain-containing protein 13; *, miRNAs can also derive from pre-mRNA introns.

**Figure 2 ijms-22-06630-f002:**
[figure not shown]
IHD-EPITRAN hypotheses (**A**). Coronary plaques signal bone marrow residing HSCs to increase proliferation promoting the efflorescence of CH and extramedullary hematopoiesis (Ly-6C^high^ monocytosis), which both seed epitranscriptomically distinct cells to the circulation. (**B**). Leukocytes and platelets patrolling in the proximity and inside the atherosclerotic plaques, ischemic myocardium, and stressed endothelium oscillate back and seed EVs to the circulation with detectable alterations in their m^6^A and A-to-I RNA signatures. (**C**). The ischemic myocardium prime patrolling leukocytes and secrete paracrine EVs encasing m^6^A and A-to-I modified RNA molecules, entering also to the circulation. *A-to-I*, adenosine-to-inosine; *CH*, clonal hematopoiesis; *EV*, extracellular vesicle; *HSC*, hematopoietic stem cell; *Ly6C*, lymphocyte antigen 6; *m^6^A*, N^6^-methyladenosine; *RBCs*, red blood cells; *TCs*, thrombocytes; *WBCs*, white blood cells.

**Figure 3 ijms-22-06630-f003:**
[figure not shown]
Outline and sample collection in the IHD-EPITRAN study. The gray scale provides an arbitrary scale for disease severity across cohorts. *STEMI*, ST-elevation myocardial infarction; *CABG*, coronary artery bypass grafting; *AVR*, aortic valve replacement; *CCTA*, coronary computed tomography angiogram; *ICA*, invasive coronary angiography; *RAA*, right atrial appendage; *IHD*, ischemic heart disease.

**Figure 4 ijms-22-06630-f004:**
[figure not shown]
Study samples with respective principal analysis methods of the IHD-EPITRAN study. *CVD*, cardiovascular disease; *FISH*, fluorescence in situ hybridization; *IHC*, immunohistochemistry; *IHD*, ischemic heart disease; *meRIP seq*, methylated RNA immunoprecipitation sequencing; *MRM*, multiple reaction monitoring; *RAA*, right atrial appendage; *UHPLC-MS/MS*; ultra-high-performance triple quadrupole liquid chromatography tandem mass spectrometry.

**Figure 5 ijms-22-06630-f005:**
[figure not shown]
Principal study cohort comparisons in the IHD-EPITRAN study. Referred outcomes are listed in Table 3 (**A**). Venn diagram-based illustration of the preferred four-partite approach, due to its highest degree of adjustments, to acquire inter-cohort comparison-based outcomes. (**B**). Three-partite comparison scheme to enable comparisons even in the possible case of delay in one cohort recruitment, which is also the case with (**C**) depicting pairwise comparisons with lest adjustments for inter-cohort outcomes. Intracohort outcomes are achieved via pairwise prospective comparisons. (**D**). Timeline for the prospective outcome comparisons. Long-term follow-up of the study cohorts I-IV could provide dimensions of detecting incident and IHD exacerbations (Section 2.6 and Discussion). Abbreviations: *AVR*, aortic valve replacement cohort III; *AVS*, aortic valve stenosis; *CABG*, coronary artery bypass grafting cohort II; *CCTA*, coronary computed tomography angiogram cohort I; *CVD*, cardiovascular disease; *IHD*, ischemic heart disease, *MACCE*, major adverse cardiovascular and cerebrovascular event; *PCI*, percutaneous coronary intervention; STEMI, ST-elevation myocardial infarction cohort I.

**Table 1 ijms-22-06630-t001:** Main goals of the IHD-EPITRAN study with brief respective descriptions. *IHD*, Ischemic heart disease.

Goal	Description
To identify IHD-specific candidate biomarkers and lay the foundation for both clinical and diagnostic efficacy studies in the future	*Corss-sectional cohort study design* Comparsion of blood RNA modifications of IHD cohorts to non-IHD cohorts *Porspective cohort study design* Comparsion of circulating RNA modifications of IHD-positive cohorts to thoes in IHD-negative cohort
To establish protocals and modify detection methods and workflows for RNA modications	Optimization of RNA isolation, type-fragmentation for modification-targeted RNA sequencing using both second and third generation methodologies
To increase the pathophysiologic knowledge of IHD	The cross-sectional and prospective comparsions of blood and right atrial appendage epitramscriptomes is expectable to provide novel insight to the IHD pathophysiology
To open venues for therapeutic development previously been disregarded due to the lack of research and methodological limitations	Identification of novel epotanscriptomic candidate blood biomarkers for IHD can provide potenial targets also for future drug development

**Table 2 ijms-22-06630-t002:** General and cohort-specific exclusion criteria for the IHD-EPITRAN study. *CCS*, Canadian cardiovascular society (for angina pectoris grading); *GFReEPI*, Glomerular filtration rate estimated with *CKD-EPI* (Chronic Kidney Disease Epidemiology Collaboration) equation; *IHD*, ischemic heart disease; *LVEF*, left ventricular ejection fraction; *LVH*, left ventricular hypertrophy; *NYHA*, New York Heart Association (for heart failure grading); *PCI*, percutaneous coronary intervention; *RR*, Scipione Riva-Rocci (eponym for sphygmomanometric blood pressure gauge).

General	Justification
Condition that limits life expectancy	May modify blood epitranscriptomes hampering reliable biomarker identification
Active inflammatory state (i.e., gout, systemic lupus erythematosus)	Cimplement, cytokines and leukocyte activation may infuence blood epitranscriptomes
Primary desease of blood or bone marrow	Expectable to alter epotranscriptomic regulation precluding reliable biomarker discovery
Major congenital heart disease of atrial fibrillation	To exclude the effects of remodelling in atrial appendges
Renal insufficiency (*GTReEPI < 45 mL/min*)	To exclude the effects of altered blood solute dynamics for reliable biomarker discovery
Uncontrolled hypertension (*RR > 180/100 mmHg*) or diabetes (*HbA1c > 60 mmol/L*), insulin us diabetes	Hight blood pressure and significant hyperglycemia damage endothelium and blood cells
Prior open-heart surgery (i.e., coronary artery bypass surgery)	To exclude very high-morbidity IHD and support the goal to identify biomarkers for early-to-moderate IHD
Other manifestations of atherosclerosis: a. Arteriosclerosis oblitierans/claudication b. Earlier stroke, cerebral hemorrhage or transient ischemic attach (TIA) c. Vascular or mixed type dementia d. Clinically releveant carotid artery stenosis e. Mesenteric ischemia	To exclude effects of other manifestations of atherosclerosis in blood epitranscriptomes as extensively as possible; Except for surveying vascular claudication, prospective investigations to exclude these manifestations will not be performed; Ankle-brachial index is recorded for any asymptomatic peripheral artery disease in cohort II
Transthoracic echocardiography: a. Cardiomyopathy (Hypertrophic/Dilated) b. Left ventricular hypertrophy (LVH) c. Clear heart failure (*i.e., LVEF < 25%)* d. Indication of atrial remodeling e. Functionally significant valve defects	To exclude remodeling effects due to intrinsic myocardial pathology, significant heart failure or valve defects; LVH is considered as an exception for the cohort III (part of pathophysiology)
**Study cohort I, patients with myocardial infarction revascularized with urgent PCI**	
Stent thrombosis, vasospastic coronary occlusion	This is IHD-focused study, myocardial infartions of other than atherothrombotic etiology are excluded
MI complications (*e.g., chordal rupture, aorthic disserction, acute heart failure, cardiogenic shock*)	To focus biomarker discovery to the IHD-induced infarction-specific epitranscriptomic alterations
Global ischemia on electrocardiogram	High rish of insufficient PCI and ischemia relievement
**Study cohort II, patients with stable IHD undergoing coronary artery bypass surgery**	
Duration of stable angina pectoris or exertional dyspneas < 1-month, crescendo angina	To exclude acute and subacute IHD related alterations in blood epitranscriptomes
Complex surgeries (e.g., valve/aneurysm repair)	To exclude other major cardiac remodeling effects
**Study cohort III, patients with stable aortic valve stenosis undergoing valve replacement surgery**	
Clinically mild-to-moderate stenosis with mild symptoms (*NYHA/CCA 0-I*)	Indicate less pronounced pathophysiology that might be reflected with blunted changes in the alterations of the blood epitranscriptomes regarding AVS
Documented IHD or complex operations	As a control cohort with non-IHD cardiac pathology, any indication of IHD will lead to exclusion
Transcatheter asortic valve implantations	To enable right atrial appendage sample collection
**Study cohort IV, patients screened negative for IHD with coronary computed tomography**	
Any prior cardiovascular disease or medication currently or in history	As critical non-IHD controls, the aim is to also recruit patients that represent overall “cardiovascular health”

**Table 3 ijms-22-06630-t003:** Planned outcomes of the IHD-EPITRAN study. Outcome 1 and outcomes 2–5 encase inter- and intra-cohort comparisons, respectively. Morbidity parameters: Section 2.3.2. *A-to-I*, adenosine-to-inosine; *AVR*, aortic valve replacement (III); *AVS*, aortic valve stenosis; *CABG*, coronary artery bypass grafting (II); *CCTA*, coronary computed tomography angiogram (IV); *m^6^A*, N^6^-methyladenosine; *IR*, ischemia-reperfusion; *PCI*, percutaneous coronary intervention; *STEMI*, ST-elevation MI (I).

Primary	Secondary
1. Study sample m6A and A-to-I profiles from the recruitment stage associating with IHD and AVS pathophysiology 1.1. Acute IR controlled for stable ishcemia, pressure overload, and homeostasis (I vs. II-III-IV) 1.2. Stable ishcemia controlled for acute IR, pressure overload, and homeostasis (II vs. I-III-IV) 1.3. Acute IR controlled for homeostasis (I vs. IV) 1.4. Pressure overload controlled for acute IR, stable ishcemia, and hemeostasis (III vs. I-II-IV)	4. Changes in the study sample m^6^A and A-to-I profiles (Recruitment vs. 3-months) associating to 4.1 Therapy effects on Pathophysiology at 3-month follow-up 4.1.1. STEMI-PCI effects (Resolution and relievement acute IR, remodelingl I vs. I) 4.1.2. IHD-CABG effects (Relievement of stable ischemia, remodeling; II vs III) 4.1.3. AVS-AVR effects (Relievement of pressure overload, remodeling; III vs. III) 4.2 All-cause mortality during 3-month follow-up 4.3 Beneficial/adverse/no-response for therapy as measured via echocardiography at 3 months 4.4 Surrogate (non-)metabolite CVD biomarker levels at recruitment, 3 months, changes between
2. Study sample m^6^A and A-to-I profiles from the recruitment stage associating with 3-moth follow-up clinicial parmeters 2.1. Cardiovascular mortality 2.2 Cardiovascular morbidity 2.3. MACCE 2.4 Cardiovascular medication increases or reductions	5. study sample m^6^A and A-to-I profiles from the recruitment stage as in outcomes 4.2.–4.5.
3. Changes in the sample m^6^A and A-to-I profiles (recruitment vs. 3-months) as in outcome 2	6. Study sample quantitative alterations in other RNA modifications as in outcomes 1–5 (2.3.8.)
	7. Plasma metabolute and non-metabolite CVD biomarkers as in outcomes 1–5 (excl.4.4) (2.3.5.)
	8. Biobank plasma and RAA sample proteomic profiles as in outcomes 1–5 (2.3.10.)
	9. Whole blood sample transcriptome-based leukpcyte profiles as in outcomes 1–5

**Table 4 ijms-22-06630-t004:** Current controller and collaborator centers of the IHD-EPITRAN study with respective main responsibilities. *A-to-I*, Adenosine-to-inosine RNA editing; *AVR*, Aortic valve replacement surgery cohort III; *AVS*, aortic valve stenosis; *CABG*, coronary artery bypass surgery cohort II; *CCTA*, coronary computed tomography angiogram cohort IV; *ICA*, invasive coronary angiography; *meRIP-seq*, methylated RNA immunoprecipitation sequencing; *m^6^A*, N^6^-methyladenosine; *PCI*, percutaneous coronary intervention; *TTE*, transthoracic echocardiography.

**Controllers**	**Main responsibility area/task**
Heart and Lung Center & Cardiac Unit, Helsinki University Hospital (HUS), Finland	Patient recruitment; clinicial evaluations; operations (PCA, CABG, AVR); imagings (ICA, CCTA, TTE); control visits; study sample collection; registry data storage and governace; sample storage
Department of Pharmacology, University of Helsinki (UH), Finland	Coordination of (1) collaboration, (2)funding acquisition and (3) competitve tendering; RNA exctraction and initial sample quality measurements; academic analyses; scientific publishing

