#### 2.3.6. Right Atrial Appendage Tissue Samples

The right atrial appendage (RAA) is often manipulated during cardiac surgery to assemble bypass circulation. Moreover, RAA has been evaluated as a safe source for cardiac tissue for both diagnostic and therapeutic applications [115]. During the IHD-EPITRAN, a small RAA tissue sample, the size of which will be guided by clinical characteristics, will be collected from the study participants in cohorts II and III to enable an organ-specific characterization of the RNA epitranscriptomes (Figure 4). The perioperatively collected RAA tissue sample will be divided into three pieces that will be stored in (1) RNAlater solution (e.g., AM7021, ThermoFisher Scientific Inc., Waltham, MA, USA) with an overnight incubation (4 °C) prior to storage (<−70 °C), (2) formalin (4%) for two weeks and then in ethanol (70%; Section 2.3.9) to prevent overfixation or (3) snap-frozen preferably with isopentane immersion and liquid nitrogen and stored (<−70 °C). The RNA isolation of the RNA later-stored RAA samples is done as previously [115]. A brief consideration of the RNA fractionation pipeline is provided in Section 2.3.7. The piece of RAA tissue snap-frozen in isopentane immersion will be a well-suited material for many histologic and omics applications, such as untargeted proteomics and spatial RNA transcriptomics (Section 2.3.9 and Section 2.3.10, respectively).

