### 2.4. Power Calculations, Cohort Comparisons, Outcomes, and Data Management

The group sizes were determined with a RNAseqPS tool designed for evaluating statistical power for sequencing studies [147]. Parameter values (false discovery rate [FDR] <0.05, total number of genes for testing 20,000, predicted prognostic genes 1500 with a minimum fold change threshold of 2 for differential expression and average read counts of 10 for prognostic genes) were derived from the applicable study regarding m^6^A during hypertrophy and HF [148]. A mean dispersion value of 0.215 was doubled (0.43) and applied for the calculations. The utilized mean was based on four assessed sequencing datasets with unrelated samples and dispersions ranging from 0.15 to 0.28 [149]. Based on the power analysis, *n* = 44 per cohort generated a power of 0.95. However, the groups sizes were fixed to *n* = 50 per cohort to address possible preanalytical errors at this initial phase. Analyses with smaller sample sizes will be first performed, followed by the larger sized analyses based on the first results and methodological optimization.

Currently, there are no reports addressing either gender or age dependent changes in neither blood nor muscle tissue epitranscriptomes. As such, the produced data in the IHD-EPITRAN study will be referenced and assessed against the typical common confounding variables, such as gender, age, comorbidities, and medication. If needed, the effects will be statistically adjusted. The IHD-EPITRAN consortium (Section 2.5) includes experts with statistics expertise and knowhow.

The study cohort comparisons used to acquire the study outcomes of the IHD-EPITRAN study are presented in Figure 5 and Table 3, respectively. The project Data Management Plan (DMP) is maintained on the webpage of the IHD-EPITRAN study (www.ihd-epitran.com).

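### Table 3 primary outcome 1 lists no IHD versus non-IHD contrast, although that comparison is the study's first goal

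*Protocol article*

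**What the plan says.** Section 2.2 assigns cohorts I and II to IHD and cohorts III and IV to non-IHD controls, with 50 patients each. Table 1 describes the cross-sectional part of the first goal as "Comparsion of blood RNA modifications of IHD cohorts to non-IHD cohorts". The Conclusions repeat the framing: "the IHD-EPITRAN study with its IHD vs. non-IHD cohort design evaluates transcriptome-wide alterations".

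Section 2.4 refers the reader to Figure 5 and Table 3 for the cohort comparisons and outcomes. The Table 3 caption says that outcome 1 holds the inter-cohort comparisons and outcomes 2 to 5 the intra-cohort ones. Outcome 1 has four lines:

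- 1.1: I vs II-III-IV, labelled acute ischemia-reperfusion (IR).
- 1.2: "1.2. Stable ishcemia controlled for acute IR, pressure overload, and homeostasis (II vs. I-III-IV").
- 1.3: I vs IV, labelled acute IR against homeostasis.
- 1.4: III vs I-II-IV, labelled pressure overload.

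The Figure 5 legend prefers a four-partite, Venn-based scheme. It offers three-partite and pairwise versions in case recruitment to one cohort is delayed, and it points to Table 3 for the outcomes. The figure itself is not available.

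On tissue, Section 2.3.6 says that an RAA sample "will be collected from the study participants in cohorts II and III to enable an organ-specific characterization of the RNA epitranscriptomes". Section 2.3.9 counts RAA tissue among the study samples, and outcome 1 is defined on study sample profiles.

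**The concern.** The headline question and the primary list do not match. A marker of IHD as such would be altered in both I and II and not in III and IV. No line of outcome 1 estimates that difference. In 1.1 and 1.2 the second IHD cohort sits on the reference side, so part of what acute and stable IHD have in common is counted as background. The stable-IHD cohort is never set against a reference made up only of non-IHD patients.

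The general IHD biomarker is therefore the signal that the listed contrasts are least suited to. If the contrast is not fixed in advance, the comparison that answers the main goal will have to be chosen after the data are seen. For RAA tissue, the one inter-cohort comparison the samples allow (II vs III) is not in outcome 1.

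**Working it through.** **Which cohorts each contrast needs**

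| Contrast | IHD cohort in the reference | Computable in RAA (II and III only) as listed |
|---|---|---|
| 1.1: I vs II-III-IV | II | no, needs I and IV |
| 1.2: II vs I-III-IV | I | no, needs I and IV |
| 1.3: I vs IV | none | no, needs I and IV |
| 1.4: III vs I-II-IV | I and II | no, needs I and IV |

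Table 3 does show a II vs III comparison at 4.1.2. That is a secondary, recruitment-to-3-month item in a block the caption calls intra-cohort, and its neighbours are I vs I and III vs III. It does not fill the gap.

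**Inputs, all from Section 2.4**

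- Error control: "false discovery rate [FDR] <0.05, total number of genes for testing 20,000".
- Effect: 1500 of these genes are taken to be truly altered, each at least two-fold.
- Depth: a mean count of 10 in the altered genes.
- Dispersion: "A mean dispersion value of 0.215 was doubled (0.43) and applied for the calculations".

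**Reproducing the plan's figure**

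- Per-test level: α* = 1500 × 0.95 × 0.05 / (18,500 × 0.95) = 0.00405, two-sided, z = 2.874.
- Wald sample size: n = (2.874 + 1.645)² × [(1 + 1/2)/10 + 2 × 0.43] / (ln 2)² = 42.9, so 43 per group.
- An exact negative binomial test gives power 0.949 at n = 43 and 0.954 at n = 44. The stated 44 per cohort for power 0.95 is reproduced. It is the figure for a simple two-cohort comparison.

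**Applying the same inputs to a shared IHD signal**

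Assumption: log effect d in both I and II, zero in III and IV. The per-patient variance on the log scale is 1/mean + 0.43. With d = ln 2 and n = 50:

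- IHD cohort: (1/20 + 0.43)/50 = 0.0096.
- Non-IHD cohort: (1/10 + 0.43)/50 = 0.0106.

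Power = Φ(effect/SE − 2.874).

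- **1.1 or 1.2, equally weighted log means:** effect d − d/3 = 2d/3 = 0.462 (1.59-fold). SE = √[0.0096 + (0.0096 + 2 × 0.0106)/9] = 0.114. Power 0.88.
- **1.1 or 1.2, pooled counts:** reference mean (20 + 10 + 10)/3 = 13.3. Effect ln(20/13.3) = ln 1.5 = 0.405. With the same SE, power 0.75.
- **1.3, I vs IV:** effect 0.693, SE = √(0.0096 + 0.0106) = 0.142. Power 0.98.
- **(I+II)/2 vs (III+IV)/2:** effect 0.693, SE = √[(2 × 0.0096 + 2 × 0.0106)/4] = 0.1005. Power above 0.999.

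At n = 44, contrasts 1.1 and 1.2 give 0.68 to 0.82; (I+II) vs (III+IV) stays above 0.999.

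**Sensitivity, 1.5-fold shared effect, n = 50.** This effect is assumed and lies below the plan's own two-fold threshold. Power is 0.24 to 0.30 for 1.1 or 1.2, 0.48 for 1.3 and 0.87 for (I+II) vs (III+IV).

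**If II must differ from each of I, III and IV separately,** the II vs I difference is zero for a shared signal. Simulated detection is then about 0.003, no more than α*.

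**The case against.** Several points on the other side have weight.

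- **Contrasts 1.1, 1.2 and 1.4 are deliberate.** They separate acute IR, stable ischemia and pressure overload, and Section 3 names acute versus chronic IHD as an aim. This stands. The contrasts are sound for those signals, and nothing here argues for dropping or demoting them.
- **Contrast 1.3 is undiluted.** A shared two-fold signal would probably be seen there, so a reader should not infer that the primary list is blind to it. But cohort I is sampled within 72 h after PCI, so 1.3 cannot tell IHD from acute infarction and reperfusion, and it uses neither II nor III.
- **Figure 5 is not available.** A reader might infer from the Venn scheme that a shared signal is subtracted. The document does not say so: a four-set diagram also has a region for what I and II share and III and IV lack, and the form of the three-cohort reference is not stated. Removal is one possible reading only. The pairwise panel might also show II vs III or II vs IV, but the legend sends the reader to Table 3 for the outcomes.
- **RAA is not without a primary analysis.** A reader might infer that it is. Primary outcome 2 is intra-cohort and can be computed in RAA within II and within III. The reduced schemes in Figure 5 would also turn 1.2 and 1.4 into II vs III, but they are offered for delayed recruitment, not for a tissue that two cohorts never provide.
- **The pooled contrast is heterogeneous.** It averages STEMI with stable disease, and aortic stenosis with people free of cardiovascular disease and medication. This is true and limits its interpretation.

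**Conclusion.** The mismatch is real: the first goal and the stated design call for I+II against III+IV, and outcome 1 contains no such contrast and no comparison of cohort II with a purely non-IHD reference. Under a pooled or averaged reference, 1.1 and 1.2 show a shared two-fold signal as 1.50- to 1.59-fold, with power 0.75 to 0.88 at 50 per cohort, where the direct contrast exceeds 0.99. This rests on equal effects in I and II, none in III and IV, and the plan's own count, dispersion and FDR inputs. For RAA, the gap is confined to the inter-cohort contrasts of outcome 1.

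This should be fixed, but it does not undermine the design. All the cohorts and samples needed are being collected, Section 3 already names the IHD versus non-IHD distinction as a use of the data, and the purpose is candidate discovery.

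**What to change.** In Table 3, outcome 1:

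- Add the equally weighted contrast (I+II)/2 vs (III+IV)/2, estimated from one model with all four cohorts.
- List II vs III as the inter-cohort contrast for RAA tissue.
- Keep 1.1 to 1.4 as the contrasts for acute-, stable- and pressure-overload-specific signals, and say whether a reference such as I-III-IV is pooled, averaged, or requires a difference from each cohort.

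The cost is a change of wording and two more contrasts to report, with a little added multiplicity. No patients, samples or assays are added. Because the new contrast averages unlike cohorts, it should be read alongside 1.1 to 1.4.
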